### Grouping and Intervention

#### Control Group

Clinical respiratory physicians will formulate standardized medication regimens for participants based on the 2023 GOLD guidelines [35] and *Chronic Obstructive Pulmonary Disease: Diagnosis and Management* by American Family Physician [36]. Participants will receive conventional pharmacological treatment throughout this trial. During this study, participants will be instructed to abstain from any form of regular traditional Chinese health-preserving exercises, defined as twice daily sessions of 30 minutes each, five times per week, according to a previous study [39]. To minimize potential attention and contact bias arising from differences in interaction frequency between groups, participants in the control group will attend the hospital once weekly, where this study’s team will manage musculoskeletal conditions unrelated to respiratory function (eg, neck, shoulder, low back, and lower limb pain). Meanwhile, we will restrict our interventions as follows: pain treatment will be limited to symptomatic management of common musculoskeletal issues, without any intervention aimed at improving exercise capacity, and analgesics will not be used. This arrangement is intended to ensure comparable clinical contact time and follow-up support between groups. In addition, the control group will receive at least five telephone follow-ups per week to record medication adherence, daily activity levels, and general health status. No respiratory exercise instruction or respiratory rehabilitation-related intervention will be provided during these contacts. In accordance with ethical considerations, participants in the control group will be offered free Liuzijue exercise guidance after completion of this trial.

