#### Liuzijue Group

Based on the control group, the same standardized medication regimens, as prescribed by clinical respiratory physicians, will be implemented. During this trial, participants will be required to perform regular Liuzijue exercise sessions according to a prescribed regimen. In the two weeks preceding the formal intervention, participants in the Liuzijue group will receive three intensive training sessions conducted by the research team to ensure mastery of the complete movements and key technical elements of the Liuzijue method through systematic instruction. High-definition demonstration videos will be distributed via mobile devices to facilitate correct performance of the prescribed exercises at home, with daily check-ins required. Each participant in the Liuzijue group will be provided with an exercise log card, on which they will record detailed information after each session, including exercise date, time, frequency, duration, location, and perceived exertion (assessed using the Borg CR-10 [Category-Ratio 10] scale, see Table 2). Weekly exercise logs will be submitted at each intensive training session. Simultaneously, researchers will maintain a logbook documenting attendance during the concentrated interventions, collect the exercise log cards, and participants will be engaged in discussions regarding their exercise performance to ensure adherence to this trial’s protocol. During supervised group exercise sessions, trial personnel who have received standardized training will provide on-site correction of participants’ movements. The degree of movement standardization will be systematically documented in the case report forms to ensure consistency of the intervention and to minimize potential impacts on this trial’s outcomes.

**Table 2. T2:** Borg CR-10^a^ rating of perceived exertion scale used to monitor exercise intensity during Liuzijue training sessions. Participants rated their perceived exertion on a scale from 0 ("nothing at all") to 10 ("maximal"), with the target intensity maintained between 4 and 6.

Rating	Description
0	Nothing at all
0.5	Very, very light
1	Very light
2	Light
3	Moderate
4	Somewhat hard
5	Hard
6	Hard
7	Very hard
8	Very hard
9	Very, very hard
10	Maximal

a CR-10: Category-Ratio 10.

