The Liuzijue exercise prescription primarily comprises eight components: the preparatory posture, the “xu” exercise to calm the liver Qi, the “he” exercise to replenish the heart Qi, the “hu” exercise to cultivate the spleen Qi, the “si” exercise to replenish the lung Qi, the “chui” exercise to replenish the kidney Qi, the “xi” exercise to regulate the Sanjiao, and the final position [40]. The Liuzijue exercise is illustrated in Figure 2. Each session lasts approximately 30 minutes and is performed twice daily, five days per week. One day per week is dedicated to supervised, intensive practice at the hospital under the guidance of a rehabilitation therapist, while the remaining six days involve home-based practice using Liuzijue instructional videos. The intervention period lasts 12 weeks.

The intervention will consist of performing two consecutive rounds of the command-version Liuzijue routine issued by the General Administration of Sport of China. All movements will be required to be executed slowly, continuously, smoothly, and with lightness, in precise coordination with the breathing rhythm—inhaling during the upward movement of the upper limbs and exhaling during their descent. The entire practice emphasizes the integration of breath regulation, body posture, and mindful concentration, with participants instructed to maintain relaxed shoulders, a stable core, and natural joint mobility. A single round of Liuzijue requires approximately 15 minutes, resulting in a total intervention duration of about 30 minutes per session. Throughout the practice, attention will be given not only to the accuracy of the movements but also to the synchronization of breathing patterns, thereby maximizing its rehabilitative benefits for the respiratory system.

Participants will be instructed by the research team to take short breaks if they experience fatigue, exhaustion, or dyspnea during exercise, and to resume once symptoms subside. Exercise intensity will be maintained between 4 and 6 on the Borg CR-10 Dyspnea Rating Scale (detailed scoring in Table 2). During exercise sessions, participants’ heart rates will be monitored with the target exercise intensity set at 60%‐80% of each participant’s age-predicted maximum heart rate.

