**Figure 2. F2:**
[figure not shown]
Illustration of the Liuzijue exercise routine. The routine consists of eight components: a preparatory posture, six-character vocalizations (“xu,” “he,” “hu,” “si,” “chui,” and “xi”), and a closing posture. Each session lasts approximately 30 minutes and is performed twice daily, 5 days per week, for 12 weeks.

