### Compliance Assessment

Adherence in the Liuzijue group will be assessed based on attendance at the weekly hospital-based supervised training sessions and completion of exercise log records. Participants who complete at least 85% of the prescribed exercise sessions will be classified as having good adherence.

In the control group, adherence will be evaluated through participation in regular telephone follow-ups, which will include confirmation of medication compliance, verification of no disease-related medication adjustments, and confirmation of abstention from traditional Chinese health exercises. Participants who complete at least 85% of the scheduled follow-up calls and continue to meet the inclusion and exclusion criteria will be classified as having good adherence.

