### Conclusions

In summary, this randomized controlled trial aims to evaluate the effects of the Liuzijue on respiratory muscle function, with a primary focus on its efficacy and safety in patients with stable COPD. As the first clinical trial specifically investigating the impact of the Liuzijue on respiratory muscle function within this population, it addresses a significant gap in the literature. The findings are expected to deepen the understanding of the mechanisms underlying traditional respiratory exercises in pulmonary rehabilitation and to provide evidence-based exercise protocols and appropriate dosing regimens for home-based rehabilitation in stable patients with COPD, thereby demonstrating clinical relevance and potential for broader application.

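### The Liuzijue dose is given as five days a week and then as one plus six days, and good adherence requires continued eligibility of controls only

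*Protocol article*

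**What the plan says.** **Dose.** The Liuzijue Group section sets sessions of about 30 minutes, "performed twice daily, five days per week", over 12 weeks. The sentence that follows divides the week into one day of supervised practice at the hospital, "while the remaining six days involve home-based practice using Liuzijue instructional videos". The Figure 2 legend repeats the first version: "performed twice daily, 5 days per week, for 12 weeks". The Control Group section tells controls to abstain from regular traditional exercise, "defined as twice daily sessions of 30 minutes each, five times per week", and the inclusion criteria use the same frequency. The Liuzijue Group section also distributes videos for home use, "with daily check-ins required", without saying on how many days a week.

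**Adherence.** The Compliance Assessment section gives each arm its own rule. For the Liuzijue group: "Participants who complete at least 85% of the prescribed exercise sessions will be classified as having good adherence". For controls: "Participants who complete at least 85% of the scheduled follow-up calls and continue to meet the inclusion and exclusion criteria" receive the same label. The control follow-up calls also confirm medication compliance, absence of disease-related medication changes and abstention from traditional Chinese exercise. These items describe what the calls cover; the sentence that awards the label does not list them.

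**Use.** The Statistical Analysis section plans an intention-to-treat analysis of all randomized participants, with per-protocol and complete-case sensitivity analyses. It does not mention the adherence label.

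**The concern.** The dose is the treatment under test, and two adjacent sentences give different numbers of days. The dose also fixes the denominator of the 85% rule, because that rule counts prescribed sessions. The Conclusions section promises "evidence-based exercise protocols and appropriate dosing regimens for home-based rehabilitation in stable patients with COPD", and the sentence in doubt is the one that sets how much of the week is home practice. Recruitment has started, so an instructor working from the second sentence could tell participants something different from one working from the first.

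The adherence rule raises a different problem. It is reasonable to measure exposure differently in each arm: sessions in one, calls and abstention in the other. Continued eligibility is not an exposure measure. It brings in clinical events after randomization, and it does so for controls only. An acute exacerbation requiring hospitalization or targeted drug treatment is an exclusion criterion. A control who has one could lose the label, while a Liuzijue participant with the same event keeps it as long as the session count is met. If such a label were used to select an analysis set, the selection would depend on a prognostic event in one arm and not in the other.

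**Working it through.** **Inputs**

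- Sessions per day: 2 (Liuzijue Group section).
- Days per week: 5 as stated (Liuzijue Group section, Figure 2 legend); 1 supervised + 6 home from the sentence after it.
- Weeks: 12 (Liuzijue Group section).
- Session length: about 0.5 h (same section).
- Good-adherence proportion: 85% (Compliance Assessment section).

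**Formulas**

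Sessions = days per week × 2 × 12. Cut = 0.85 × sessions, rounded up to a whole session.

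**The stated dose**

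- Sessions: 5 × 2 × 12 = 120, or 120 × 0.5 = 60 h.
- Cut: 0.85 × 120 = 102, so 18 sessions may be missed.

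**The next sentence taken literally**

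- Days: 1 + 6 = 7, not 5.
- Sessions: 7 × 2 × 12 = 168, or 168 × 0.5 = 84 h.
- Cut: 0.85 × 168 = 142.8, so 143.

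**Comparison**

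- 168 / 120 = 1.40, so the literal sentence implies 40% more sessions.
- A participant who completes every session of the five-day plan reaches 120 / 168 = 71.4% of the seven-day count and fails the 85% rule.
- A participant exactly at the five-day cut reaches 102 / 168 = 60.7%.

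A split into supervised and home sessions is not calculated here. It would require knowing whether both sessions on the hospital day are supervised, and the article does not say.

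**Which number is meant**

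The five-day frequency appears in the Liuzijue Group section and the Figure 2 legend, and it matches the definition of regular practice in the inclusion criteria and the Control Group section. The six home days appear once, in a sentence about where practice takes place. The daily check-ins fit either version. Five days is the intended dose; with one supervised day, 5 − 1 = 4 exercise days remain for home.

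**The adherence rule, side by side**

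| Condition for good adherence | Liuzijue group | Control group |
|---|---|---|
| Contact or exposure | at least 85% of prescribed sessions | at least 85% of scheduled calls |
| Continued eligibility | not stated | required |

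No arithmetic applies. How strict the control condition is depends on how it is read. If any exacerbation after randomization breaks eligibility, the control loses the label for good. If eligibility is judged at a point in time, a resolved exacerbation would not count. The text does not say which reading holds.

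**The case against.** The strongest reply on dose is that this is a slip which the document itself resolves. Only one session frequency is ever stated, and it is five days. The odd sentence may mean only that home practice falls somewhere within the other six days of the week. Nothing suggests that anyone would apply a cut of 143. Most of this stands: five days is clearly intended, and 168 and 143 show only what the sentence would imply if followed. What remains is that the sentence, as written, has all six days involve home practice, and no other text corrects it.

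The reply on adherence is that the label has no stated analytic use, and that defining a per-protocol set is commonly left to a fuller document. That also stands. The lack of such a definition is not a fault here; the objection is only to the unequal rule that is stated. A further reply is that controls need some condition against taking up traditional exercise, which cannot apply to the treated arm. That is fair, and it supports naming abstention explicitly instead of importing the whole eligibility list.

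A reader might go further and infer that the per-protocol walking distance comparison is biased by some number of metres. The document does not support this. It would require the label to define the set, the strict reading of eligibility, an exacerbation rate and an effect of exacerbation on walking distance that the article does not give, and affected Liuzijue participants who still complete at least 102 sessions. An exacerbation could plausibly cost more than the 18 sessions that may be missed, in which case that participant would lose the label too.

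**Conclusion.** Both points hold, at low priority.

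- **Dose.** The stated treatment contradicts itself in adjacent sentences: five days, then 1 + 6 = 7. The five-day plan of 120 sessions, with a cut of 102, is the intended one. A reader might infer that participants are prescribed 168 sessions; the repeated five-day frequency speaks against that.
- **Adherence.** The classification rule places a condition tied to events after randomization on controls only. This is an asymmetry in the text and does not depend on any assumed event rate.

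The intention-to-treat analysis is untouched by either point. The per-protocol sensitivity analysis would be biased only if the label defines its set, and the direction and size of any bias cannot be quantified from the document.

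**What to change.** **Liuzijue Group section.** Replace the sentence with wording such as: *One day per week is supervised at the hospital and the remaining four exercise days are home-based.* The clinical team should confirm it.

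**Compliance Assessment section, Liuzijue group.** State that the 85% is counted against 120 sessions, so that good adherence means at least 102.

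**Compliance Assessment section, controls.** Choose one of two forms:

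1. Delete the continued-eligibility clause and define control adherence as at least 85% of calls plus confirmed abstention from traditional Chinese exercise. This is the simpler form. Abstention has to be written into the rule, because at present it is only an item covered by the calls.
2. Apply the same clinical conditions after randomization to both arms. List which criteria count, say whether a resolved exacerbation counts, and omit the no-traditional-exercise criterion for the Liuzijue group, whose treatment is such an exercise.

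**Cost.** Wording only. Exercise logs, call records and adverse events are already collected. At submission 8 Liuzijue and 15 control participants were enrolled; the team should check which frequency those 8, and any enrolled since, were told. The change should be made before the analysis planned for January 2027.

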**Figure 2. F2:**
[figure not shown]
Illustration of the Liuzijue exercise routine. The routine consists of eight components: a preparatory posture, six-character vocalizations (“xu,” “he,” “hu,” “si,” “chui,” and “xi”), and a closing posture. Each session lasts approximately 30 minutes and is performed twice daily, 5 days per week, for 12 weeks.

### Outcome Measurement

The outcome measurements for both groups and the specific assessment time points are detailed in Table 1.

### Primary Outcome Measures

#### Overview

The primary outcomes of this trial are surface electromyography (sEMG) and 6MWT.

#### sEMG

sEMG is a noninvasive technique that allows real-time and precise assessment of the electrical activity of superficial muscles, thereby providing an objective reflection of muscle recruitment and functional status. Previous studies [41,42] have demonstrated a high correlation between sEMG and invasive electromyography (EMG) signals, while effectively avoiding the stress responses induced by traditional invasive methods, which facilitates the acquisition of more reliable experimental data.

In this study, a 16-channel NORAXON Wireless EMG system (NORAXON Wireless EMG) combined with EMGworks Acquisition 4.5 (Delsys) software will be used to noninvasively evaluate changes in respiratory muscle strength in patients with COPD before and after the intervention. The primary parameters measured will include the root mean square of the EMG signal, averaged EMG, and mean power frequency. Root mean square and averaged EMG are used to quantify the intensity of muscle activation, while mean power frequency is used to assess muscle fatigue [43]. The muscles monitored include the sternocleidomastoid, trapezius, intercostal muscles, diaphragm, rectus abdominis, external oblique, internal oblique, transversus abdominis, and multifidus. Electrode placement strictly follows the SENIAM (Surface Electromyography for the Non-Invasive Assessment of Muscles) protocol, with recommended locations for respiratory muscles summarized in Table 3 [43-47]. Before signal acquisition, the skin will be thoroughly cleansed with alcohol to reduce impedance and ensure high-quality data.

**Table 3. T3:** Electrode placement locations for respiratory muscles based on the SENIAM^a^ protocol.

No.	Muscle	Electrode placement
1	Sternocleidomastoid	The midpoint of the prominently bulging muscle on the anterolateral neck when the head is turned to the opposite side
2	Trapezius	The midpoint between C7^b^ and the acromion
3	Intercostal muscles	Two finger-breadths lateral to the sternum, at the midpoint between the second and third ribs
4	Diaphragm	The intersection of the midclavicular line and the 8th rib
5	Rectus abdominis	Two finger-breadths lateral to the umbilicus
6	External oblique	The intersection of the anterior axillary line and the 10th rib
7	Internal oblique	Located 2 cm superior to the ASIS^c^
8	Transversus abdominis	2 cm medial to the ASIS, slightly below the horizontal line of the umbilicus
9	Multifidus	The junction between the middle $\frac{1}{3}$ and medial $\frac{1}{3}$ of the line from PSIS^d^ to L5^e^

a SENIAM: Surface Electromyography for the Non-Invasive Assessment of Muscles.

b C7: the seventh cervical vertebra.

c ASIS: anterior superior iliac spine.

d PSIS: posterior superior iliac spine.

e L5: the fifth lumbar vertebra.

The sEMG assessment will consist of static and dynamic tests. In the static test, participants will stand quietly while EMG signals are recorded for 5 seconds at rest, at the end of maximal inspiration, and at the end of maximal expiration, with each condition repeated three times at two-minute intervals. The dynamic test will involve a 10-meter walking trial, during which participants are instructed to walk as fast as possible along a corridor while both walking time and EMG signals are recorded simultaneously. The electrode placement for sEMG is illustrated in Figure 3. The sEMG data will be collected in week 0 and week 13.

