Overall, the anticipated findings are expected not only to provide high-quality evidence to support the optimization and individualization of clinical pulmonary rehabilitation programs, but also to offer a more in-depth and systematic theoretical interpretation of the mechanisms through which traditional Chinese health-preserving exercises and rehabilitation techniques exert their effects in COPD rehabilitation.

This study describes the protocol of a randomized controlled trial designed to evaluate the effects of Liuzijue exercise on respiratory muscle function and functional outcomes in patients with COPD, while further elucidating its role in improving the status of specific respiratory muscles and characterizing the recruitment patterns of major respiratory muscle groups. These findings will provide an important theoretical basis for the application of traditional Chinese health-preserving exercises in respiratory function enhancement. Building on this, this study will also focus on evaluating the therapeutic effects and safety of Liuzijue in patients with COPD-related respiratory muscle dysfunction.

Several limitations should be noted. First, this study population is limited to patients with stable COPD, excluding those with varying degrees of disease severity, which may restrict the generalizability of the findings. Second, this study has certain limitations in the assessment of upper limb muscle parameters, which may not fully capture the effects of Liuzijue exercise on the accessory respiratory muscles of the upper limbs. Third, there is currently no highly precise kinematic tool capable of directly measuring respiratory muscle changes; therefore, the kinematic parameters in this study remain limited. Finally, due to the inherent characteristics of the intervention, a double-blind trial is not feasible, which may introduce a potential risk of bias. Despite these limitations, the rigorous design and comprehensive outcome measures are expected to yield clinically meaningful evidence.

The findings of this study will be disseminated through peer-reviewed journal publications, and standardized instructional videos will be developed to facilitate learning and application among community-based patients.

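### Table 3 gives the transversus abdominis its own surface electrode site within the co-primary sEMG outcome, but a surface signal there cannot be attributed to that muscle alone.

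*Protocol article*

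**What the plan says.** The Overview under Primary Outcome Measures states: "The primary outcomes of this trial are surface electromyography (sEMG) and 6MWT". So whatever sEMG records carries primary weight.

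The sEMG section introduces the technique as one that "allows real-time and precise assessment of the electrical activity of superficial muscles". It then lists nine muscles, the last six being the "diaphragm, rectus abdominis, external oblique, internal oblique, transversus abdominis, and multifidus". Table 3 gives each of the nine its own electrode site. Three rows matter here:

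- Row 8, transversus abdominis: "2 cm medial to the ASIS, slightly below the horizontal line of the umbilicus".
- Row 7, internal oblique: "Located 2 cm superior to the ASIS".
- Row 4, diaphragm: "The intersection of the midclavicular line and the 8th rib".

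The recorder is "a 16-channel NORAXON Wireless EMG system"; the article does not map channels to muscles. It supports the method by saying that earlier studies found sEMG to correlate highly with invasive EMG, without naming a muscle, and by saying that placement follows the SENIAM scheme.

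Principal Findings sets the interpretive aim at muscle level: "further elucidating its role in improving the status of specific respiratory muscles".

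**The concern.** The protocol describes a method for superficial muscles and then uses it, within a primary outcome, to report on a muscle that is not superficial. If the plan is followed as written, activity from an overlying layer of the abdominal wall could be published as a change in the transversus abdominis. The stated aim is to say something about specific muscles, so the label on each site is part of the conclusion. A wrong label cannot be corrected by the statistical model, because the model sees only the recorded amplitude or frequency and not the layer it came from.

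**Working it through.** The plan gives no figure for sEMG to reproduce: it states no sEMG effect size or SD, and its sample size rests on the 6-minute walk test. The check is therefore a comparison of statements plus a count.

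**Step 1: scope against use.** The sEMG section limits the method to superficial muscles. The muscle list in the same section and Table 3 row 8 treat the transversus abdominis as separately measured. No sentence reconciles the two.

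**Step 2: depth.** The article does not say which muscles are deep. This step uses basic anatomy: the transversus abdominis is the deepest layer of the lateral abdominal wall and lies under the internal oblique. An electrode on the skin at row 8 records through whatever lies above that muscle. The argument needs only that some overlying muscle contributes. It does not need to say which layer contributes most.

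**Step 3: the neighbouring site.** Row 7 (internal oblique) and row 8 (transversus abdominis) are both described from the ASIS, so both sit on the lower lateral abdominal wall. The table labels them as two muscles, but nothing in the article shows that row 8 records the deeper one to the exclusion of the one above it.

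**Step 4: the support offered.** The correlation with invasive EMG is stated in general terms for no named muscle, and it follows a sentence that confines the method to superficial muscles. Following a placement scheme fixes where on the skin the electrode goes, not how deep it reads.

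**Step 5: extent.**

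- Muscles affected: 1 of 9 = 11%.
- Possible readouts, if every muscle yields all three parameters (root mean square, averaged EMG, mean power frequency) in all three static conditions and the one walking test: 9 × 3 × (3 + 1) = 108.
- Share labelled transversus abdominis: 1 × 3 × 4 = 12, and 12/108 = 11%.

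The article does not say which of these readouts form the co-primary endpoint, so 12 of 108 is a count of what the described tests could yield, not of planned hypothesis tests.

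**The case against.** The best defence has three parts.

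*The article cites validation and placement sources.* These cannot be seen here and may cover the lower abdominal wall. That rules out saying that the signal holds no information about the transversus abdominis. It does not rescue the label, because the article's own sentence about correlation names no muscle.

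*Reporting and crosstalk may be handled elsewhere.* A condensed article can leave channel pooling to the full protocol or the analysis plan. That is fair, and the absence of a crosstalk method is not the point. The muscle name and the site are stated in the article, and they conflict with its description of the method.

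*The muscle-level aim names no muscle.* True: Principal Findings does not mention the transversus abdominis, and the Introduction names the diaphragm and intercostals as the evidence gap. This keeps the point small. It does not remove it, because the transversus abdominis is still listed by name in a co-primary outcome.

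A reader might go further and infer that several channels fail, namely the diaphragm, internal oblique and multifidus, and that all conclusions about the diaphragm should be barred. The documents do not support this. They contain nothing that shows the diaphragm site fails. The internal oblique cannot be counted as a deep muscle and also be the overlying source at row 8. No rule is available for sorting the remaining muscles by depth. A reader might also argue that rows 7 and 8 are so close that they duplicate one signal and should be merged. Row 8 has a second clause, referring to the level of the umbilicus, that leaves its height relative to the ASIS open, and the placement figure is not shown, so the distance between the sites cannot be fixed from the text.

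**Conclusion.** The point holds for one site. On the protocol's own description of sEMG, a change at row 8 of Table 3 cannot be attributed to the transversus abdominis alone, and the article offers no muscle-specific support for doing so. The size is 1 of 9 muscles (11%) in one of two co-primary outcomes. The 6-minute walk test and its analysis are not affected.

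The conclusion rests on one assumption from outside the text, the layering of the lateral abdominal wall, and on reading each row of Table 3 as a separately reported measurement.

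For the diaphragm site the supportable statement is weaker: it is a surface recording that may include overlying chest-wall muscle, and the article gives no validation for that site by name. That calls for a caution in reporting, not for removing the channel or giving up the diaphragm question.

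**What to change.** 1. In Table 3 and in the definition of the sEMG outcome, relabel row 8 as a combined internal oblique/transversus abdominis signal (lower lateral abdominal wall).
2. Do not count or report the transversus abdominis as a separate co-primary muscle, and draw no conclusion specific to it from this site.
3. Keep the diaphragm channel (row 4) and describe it, wherever it is reported, as a surface signal that may include overlying chest-wall muscle.
4. Leave row 7 and the other rows as they are.

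The cost is one muscle-specific claim out of nine. No electrode moves, no visit is added and no recorded data are discarded. Because the change touches the wording of a co-primary outcome after recruitment began (23 of 76 enrolled at submission), it should be made as a dated amendment before the analysis planned for January 2027.
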